## Abstract

**Background:**

Approximately 40% of Emergency Department (ED) patients with chest pain meet diagnostic criteria for panic-related anxiety, but only 1–2% are correctly diagnosed and appropriately managed in the ED. A stepped-care model, which focuses on providing evidence-based interventions in a resource-efficient manner, is the state-of-the art for treating panic disorder patients in medical settings such as primary care. Stepped-care has yet to be tested in the ED setting, which is the first point of contact with the healthcare system for most patients with panic symptoms.

**Methods:**

This multi-site randomized controlled trial (RCT) aims to evaluate the clinical, patient-centred, and economic effectiveness of a stepped-care intervention in a sample of 212 patients with panic-related anxiety presenting to the ED of Singapore’s largest public healthcare group. Participants will be randomly assigned to either: 1) an enhanced care arm consisting of a stepped-care intervention for panic-related anxiety; or 2) a control arm consisting of screening for panic attacks and panic disorder. Screening will be followed by baseline assessments and blocked randomization in a 1:1 ratio. Masked follow-up assessments will be conducted at 1, 3, 6, and 12 months. Clinical outcomes will be panic symptom severity and rates of panic disorder. Patient-centred outcomes will be health-related quality of life, daily functioning, psychiatric comorbidity, and health services utilization. Economic effectiveness outcomes will be the incremental cost-effectiveness ratio of the stepped-care intervention relative to screening alone.

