**Discussion:**

This trial will examine the impact of early intervention for patients with panic-related anxiety in the ED setting. The results will be used to propose a clinically-meaningful and cost-effective model of care for ED patients with panic-related anxiety.

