## Background

Panic disorder affects approximately 2% of the general population worldwide [1], and is associated with significant disability [2], high medical costs [3], and poor long-term outcomes [4]. The cardinal symptom of panic disorder is recurrent panic attacks consisting of symptoms such as chest pain, heart palpitations, shortness of breath, and other physical symptoms that may be interpreted by the sufferer as dangerous and indicative of a serious medical problem. Due to this misconception, patients with panic attacks often seek care in the emergency department (ED), rather than in psychiatric clinics or other mental health settings [5, 6]. A recent survey found that 34.5% of ED patients with non-cardiac chest pain met diagnostic criteria for panic attacks and 77% of these patients reported that they had visited the ED following a panic attack [7]. Despite the fact that up to 40% of ED patients with chest pain meet criteria for panic-related anxiety (i.e., panic attacks or panic disorder), only 1–2% of these patients are typically evaluated and treated for anxiety in this setting [6, 8]. Follow-up studies indicate that ED patients presenting with chest pain and panic attacks are at increased risk for developing panic disorder following discharge from the ED [9, 10]. Earlier identification and treatment of panic attacks when patients first visit the ED may help to prevent later progression to panic disorder, as well as poor long-term clinical outcomes and unnecessary recurrent ED visits for panic symptoms.

International clinical practice guidelines support the use of cognitive behavioural therapy (CBT) and antidepressant medications as first-line treatments for patients with panic disorder [11–15]. CBT for panic-related anxiety involves patient education regarding the nature and physiology of the panic response, techniques designed to alter catastrophic misinterpretations of panic symptoms, and gradual exposure to panic-related body sensations and avoided situations. Although pharmacotherapy and CBT show similar results in terms of short-term treatment efficacy, CBT has a more durable and sustained response following treatment discontinuation. It is also more cost-effective, has no serious adverse side effects, and fewer dropouts compared to pharmacotherapy [16, 17]. Furthermore, brief CBT protocols (5–7 sessions) have shown clinical and patient-centred outcomes that are equivalent to lengthier protocols [18].

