### Specific aims

*Aim 1 (Primary):* To evaluate the clinical effectiveness of a stepped-care intervention for ED patients with panic-related anxiety compared to screening alone.

*Outcomes under Aim 1:* The primary outcome under Aim 1 will be clinician-rated severity of panic symptoms, measured using the Panic Disorder Severity Scale (PDSS) [30] and the Clinical Global Impression Scale (CGI) [31]. Panic disorder will be diagnosed using the Structured Clinical Interview for DSM-5 (SCID) [32].

*Aim 2:* To evaluate the patient-centred effectiveness of a stepped-care intervention for ED patients with panic-related anxiety compared to screening alone.

*Outcomes under Aim 2:* We will examine health-related quality of life using the 12-item Short Form Health Survey (SF-12) [33], and the EuroQoL–5 Dimension (EQ-5D) [34]. We will assess psychiatric comorbidity using the Psychiatric Diagnostic Screening Questionnaire (PDSQ) [35], and healthcare utilization for panic-related symptoms (ED visits and hospital admissions) based on electronic medical record data in the 12 months following the intervention.

*Aim 3:* To evaluate the incremental cost-effectiveness of a stepped-care intervention for ED patients with panic-related anxiety compared to screening alone, from the health system perspective.

*Outcomes under Aim 3:* We will calculate the incremental cost-effectiveness ratio (ICER) of stepped-care intervention relative to screening alone, at 12 months from baseline. Direct healthcare costs will be calculated from electronic billing records and the effectiveness of the intervention will be assessed based on the conversion of SF-12 form to a quality of life weight using the Short Form Health Survey 6D (SF-6D) algorithm [36].

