*Inclusion Criteria:* 1. Diagnosis of panic attack or panic disorder confirmed by the SCID interview 2. Willing to enter randomized trial	*Exclusion Criteria:* 1. Does not meet criteria for panic attack or panic disorder based on the SCID interview 2. Received CBT for panic symptoms in the last 12 months 3. Unwilling to enter randomized trial

In order to maximize generalizability to the broad group of patients with panic symptoms who present to the ED, we will not exclude patients who have received other types of psychotherapy for panic symptoms or those who are being treated with antidepressant medications. However, we will assess for these treatments at each time point and we will control for ancillary treatments in subsequent analyses. Patients who have received CBT for panic symptoms in the prior 12 months will be excluded.

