### Randomization

Patients will be randomly allocated to one of the two arms based on a code generated using the open-source software R (https://www.r-project.org) and contained within sequential sealed envelopes. We will stratify the participants by the diagnosis of panic attack or panic disorder. Within each stratum, we will apply a permuted block randomization scheme with a block size of 4 and a 1:1 randomization ratio between the screening alone (SCREEN) or stepped-care intervention (STEP) arms. This permuted block randomization will ensure balance in the trial. The randomization block will be generated before commencing the study at the various sites. The study coordinator will proceed to open the randomisation envelopes to reveal the allocation only after a patient has been enrolled in the trial.

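### The pooled rate of panic disorder mixes new onset with persistence, so it cannot show whether progression to panic disorder was prevented

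*Protocol article*

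**What the plan says.** All references are to the protocol article.

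- **Background.** ED patients with chest pain and panic attacks "are at increased risk for developing panic disorder following discharge from the ED". Treating panic attacks earlier "may help to prevent later progression to panic disorder, as well as poor long-term clinical outcomes and unnecessary recurrent ED visits for panic symptoms".
- **Table 1, Stage 2 inclusion.** "Diagnosis of panic attack or panic disorder confirmed by the SCID interview". Table 1 sets no limit on illness duration. The text below it excludes recent CBT for panic but allows other psychotherapy and antidepressants.
- **Abstract, Methods.** "Clinical outcomes will be panic symptom severity and rates of panic disorder". The rate is not restricted by baseline diagnosis.
- **Randomization.** "We will stratify the participants by the diagnosis of panic attack or panic disorder".
- **Table 2.** The SCID panic module is done at baseline and at 1, 3, 6 and 12 months.
- **Data analysis, Aim 1.** The mixed model for the primary outcome has treatment, visit and their interaction as fixed effects. SCID diagnoses are to be handled in the same way. No term for baseline diagnosis is listed and no analysis by stratum is described.

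**The concern.** A patient who has panic disorder at randomisation cannot progress to it. In that stratum a positive SCID at follow-up means persistence or relapse; in the panic-attack stratum it means onset. The plan separates the two groups when it allocates treatment, but the SCID outcome it describes adds them together.

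Two things are at stake. A lower overall rate in STEP could come entirely from remission of established disorder and still be read as the prevention that the Background hopes for. Conversely, a real preventive effect would be diluted by patients who cannot show it.

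**Working it through.** **The plan's own figure.** The sample size concerns the PDSS and is not in dispute. With d = 0.516, two-sided alpha 0.05 and 90% power, n per arm = 2 × (1.960 + 1.282)² / 0.516² = 78.9, so 79; the plan states 80. Power at 80 per arm by the t-test is 90.0%. Allowing for 25% attrition, 79 / 0.75 = 105.3, so 106 per arm and 212 in total, as stated. The article gives no figure for the panic disorder rate.

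**Inputs assumed, because the article gives none.** Share with panic disorder at baseline, f: 30%, 50% or 70%. SCREEN persistence among those with the disorder: 70%. SCREEN onset among those without it: 30%.

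**Step 1: what the pooled rate measures.**

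Pooled rate = f × persistence + (1 − f) × onset.

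One arm difference in this sum does not reveal which component moved. That is true for any mix that includes both groups.

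**Step 2: the same result from opposite causes.**

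| f | SCREEN pooled | STEP pooled | Remission only (onset stays 30%) | Prevention only (persistence stays 70%) |
|---|---|---|---|---|
| 50% | 0.5 × 70 + 0.5 × 30 = 50% | 40% | persistence 70% to 50% | onset 30% to 10% |
| 30% | 0.3 × 70 + 0.7 × 30 = 42% | 32% | persistence 70% to 36.7% | onset 30% to 15.7% |

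At f = 70% the SCREEN rate is 0.7 × 70 + 0.3 × 30 = 58%. Remission alone gives a 10-point fall if persistence drops to 55.7%. Prevention alone cannot, because abolishing onset altogether removes only 0.3 × 30 = 9 points.

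**Step 3: dilution.** If onset halves from 30% to 15% and persistence does not change, the pooled difference is (1 − f) × 15 points: 10.5, 7.5 or 4.5 points for f = 30%, 50% or 70%.

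**Step 4: precision within the at-risk stratum.** Evaluable patients per arm = (1 − f) × 80. Power uses the normal approximation for two proportions, with p̄ the mean of the two rates:

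z = [|p1 − p2| × √n − 1.96 × √(2p̄(1 − p̄))] / √(p1(1 − p1) + p2(1 − p2)), and power = Φ(z).

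For f = 50% and 30% versus 15%: z = (0.15 × √40 − 1.96 × √0.34875) / √0.3375 = −0.36, so power is 36%.

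| f | n per arm | 30% vs 15% | 30% vs 10% |
|---|---|---|---|
| 30% | 56 | 48% | 76% |
| 50% | 40 | 36% | 61% |
| 70% | 24 | 23% | 41% |

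**The case against.** The strongest reply is that the plan never sets out to prove prevention. Aim 1 is clinical effectiveness in patients with panic-related anxiety. Progression appears in a hedged Background sentence, beside long-term outcomes and repeat ED visits, and the Study rationale section does not mention it. This stands, and it limits how serious the point is.

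A reader might go further and infer that the pooled rate is invalid, or that every conclusion about early intervention depends on the panic-attack stratum. The article supports neither.

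- Prevalence of panic disorder among all randomised patients is a proper intention-to-treat contrast, with randomisation stratified by baseline diagnosis. Remission of established disorder would be a genuine success under Aim 1.
- The Abstract's Discussion says: "This trial will examine the impact of early intervention for patients with panic-related anxiety in the ED setting". The Background defines panic-related anxiety as covering panic attacks or panic disorder, so that sentence includes treating existing disorder. It makes no claim about prevention.

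Nor should the pooled outcome be replaced. Step 4 shows how little power the at-risk stratum would have.

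It can also be said that stratum analyses usually belong in the statistical analysis plan, which is not shown. That plan may well contain them, and their absence from an article is not the complaint. The point is that the outcome and model as described mix two events, one of which the article uses to motivate the trial. This part of the objection softens the point but does not remove it.

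**Conclusion.** The point holds in a limited form. As described, the SCID outcome answers whether fewer ED patients have panic disorder at follow-up under STEP than under SCREEN. It does not answer whether progression from panic attacks to panic disorder was prevented.

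That ambiguity is structural and does not depend on the assumed rates. Its size does: the 10-point pooled difference with opposite explanations, and the shrinkage of a 15-point preventive effect to between 4.5 and 10.5 points, rest on an assumed baseline mix and assumed persistence and onset rates. The primary PDSS analysis and the sample size are unaffected. This is an improvement worth making to a secondary clinical outcome and to the wording of conclusions; it is not a flaw in the trial's main comparison.

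**What to change.** Keep the pooled panic disorder rate and the overall PDSS contrast. Before arm-level results are seen, add two secondary outcomes, both at 12 months and both defined on the randomisation strata:

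1. SCID panic disorder among those randomised with panic attack only.
2. Absence of SCID panic disorder among those randomised with panic disorder.

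Add baseline diagnosis and its interaction with treatment to the SCID model, in a form that yields the 12-month arm contrast within each stratum. Report each contrast as an estimate with its confidence interval. Let statements about preventing progression to panic disorder rest on outcome 1; other statements about early intervention need no such restriction.

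**Cost.** Wording and analysis only: the strata and the SCID at every visit are already planned, and no extra patients or visits are needed. The price is low precision in each stratum. In the middle case of Step 4 (40 per arm, 30% versus 15%), the 95% interval for the difference extends about 1.96 × √((0.21 + 0.1275) / 40) = 0.18, or 18 points, either side. The plan should therefore say in advance that these are estimates and not confirmatory tests, and that a claim of prevention may not be supportable.

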**Discussion:**

This trial will examine the impact of early intervention for patients with panic-related anxiety in the ED setting. The results will be used to propose a clinically-meaningful and cost-effective model of care for ED patients with panic-related anxiety.

**Trial registration:**

ClinicalTrials.gov NCT03632356. Retrospectively registered 15 August 2018.

## Background

Panic disorder affects approximately 2% of the general population worldwide [1], and is associated with significant disability [2], high medical costs [3], and poor long-term outcomes [4]. The cardinal symptom of panic disorder is recurrent panic attacks consisting of symptoms such as chest pain, heart palpitations, shortness of breath, and other physical symptoms that may be interpreted by the sufferer as dangerous and indicative of a serious medical problem. Due to this misconception, patients with panic attacks often seek care in the emergency department (ED), rather than in psychiatric clinics or other mental health settings [5, 6]. A recent survey found that 34.5% of ED patients with non-cardiac chest pain met diagnostic criteria for panic attacks and 77% of these patients reported that they had visited the ED following a panic attack [7]. Despite the fact that up to 40% of ED patients with chest pain meet criteria for panic-related anxiety (i.e., panic attacks or panic disorder), only 1–2% of these patients are typically evaluated and treated for anxiety in this setting [6, 8]. Follow-up studies indicate that ED patients presenting with chest pain and panic attacks are at increased risk for developing panic disorder following discharge from the ED [9, 10]. Earlier identification and treatment of panic attacks when patients first visit the ED may help to prevent later progression to panic disorder, as well as poor long-term clinical outcomes and unnecessary recurrent ED visits for panic symptoms.

International clinical practice guidelines support the use of cognitive behavioural therapy (CBT) and antidepressant medications as first-line treatments for patients with panic disorder [11–15]. CBT for panic-related anxiety involves patient education regarding the nature and physiology of the panic response, techniques designed to alter catastrophic misinterpretations of panic symptoms, and gradual exposure to panic-related body sensations and avoided situations. Although pharmacotherapy and CBT show similar results in terms of short-term treatment efficacy, CBT has a more durable and sustained response following treatment discontinuation. It is also more cost-effective, has no serious adverse side effects, and fewer dropouts compared to pharmacotherapy [16, 17]. Furthermore, brief CBT protocols (5–7 sessions) have shown clinical and patient-centred outcomes that are equivalent to lengthier protocols [18].

A small number of studies have evaluated the impact of educational, pharmacological, and CBT interventions for patients with panic disorder initiated in the ED [19–21]. Although sample sizes were modest, the results have been promising with respect to clinical outcomes [19–21] and incremental cost-effectiveness [20, 22]. Meta-analytic data indicates that patients with panic symptoms have the best response to psychological interventions when implemented early in the course of illness [23]. However, only a few studies have tested the impact of early interventions on ED patients with panic attacks [24–26]. Participants who received psychoeducation and exposure instruction reported significant improvements with respect to depression symptoms and frequency of panic attacks [24], as well as decreased frequency of subsequent ED visits, and increased participation in psychiatric outpatient treatment [25, 26].

### Study rationale

The current treatment gap for ED patients with panic-related anxiety constitutes a significant public health problem. It highlights the need to implement targeted early interventions that can improve clinical and patient-centred outcomes while reducing panic-related emergency medicine costs [27]. Tailored treatment via a ‘stepped-care’ model is now recommended as the state-of-the art for treating patients with panic-related anxiety [14] (see Fig. 1). In a stepped-care model, all patients start with a low-intensity evidence-based intervention. Progress is monitored and patients who do not respond adequately are subsequently ‘stepped up’ to a higher intensity treatment. Preliminary studies of stepped-care for panic disorder in primary care clinics have shown clinical effectiveness, patient-centred effectiveness, and cost-effectiveness relative to usual care [28, 29]. However, stepped-care for panic-related anxiety has yet to be tested in the ED setting, which is the first point of contact with the healthcare system for most patients with panic symptoms [6].

**Fig. 1 Fig1:**
[figure not shown]
Recommended interventions at each level of a stepped-care model for treatment of patients with panic-related anxiety [14]

### Overall objectives

The main objectives of this study are to evaluate the clinical, patient-centred, and economic effectiveness of stepped-care for ED patients with panic-related anxiety, using a randomized controlled trial (RCT) design. The RCT will have two arms: 1) a treatment arm consisting of stepped-care intervention for panic-related anxiety (enhanced care pathway); and 2) a control arm consisting of screening for panic-related anxiety and discharge at the ED (usual care). In addition to the baseline assessment, the study will include follow-up visits at 1, 3, 6, and 12 months.

### Specific aims

*Aim 1 (Primary):* To evaluate the clinical effectiveness of a stepped-care intervention for ED patients with panic-related anxiety compared to screening alone.

*Outcomes under Aim 1:* The primary outcome under Aim 1 will be clinician-rated severity of panic symptoms, measured using the Panic Disorder Severity Scale (PDSS) [30] and the Clinical Global Impression Scale (CGI) [31]. Panic disorder will be diagnosed using the Structured Clinical Interview for DSM-5 (SCID) [32].

*Aim 2:* To evaluate the patient-centred effectiveness of a stepped-care intervention for ED patients with panic-related anxiety compared to screening alone.

*Outcomes under Aim 2:* We will examine health-related quality of life using the 12-item Short Form Health Survey (SF-12) [33], and the EuroQoL–5 Dimension (EQ-5D) [34]. We will assess psychiatric comorbidity using the Psychiatric Diagnostic Screening Questionnaire (PDSQ) [35], and healthcare utilization for panic-related symptoms (ED visits and hospital admissions) based on electronic medical record data in the 12 months following the intervention.

*Aim 3:* To evaluate the incremental cost-effectiveness of a stepped-care intervention for ED patients with panic-related anxiety compared to screening alone, from the health system perspective.

*Outcomes under Aim 3:* We will calculate the incremental cost-effectiveness ratio (ICER) of stepped-care intervention relative to screening alone, at 12 months from baseline. Direct healthcare costs will be calculated from electronic billing records and the effectiveness of the intervention will be assessed based on the conversion of SF-12 form to a quality of life weight using the Short Form Health Survey 6D (SF-6D) algorithm [36].

## Methods and analysis

### Study design

This 12-month superiority trial will follow a two-stage parallel group multi-site RCT design. Screening will be done at the first stage, followed by baseline assessments and block randomization in a 1:1 ratio to either the screening alone (SCREEN) or stepped-care (STEP) arms at the second stage. Only patients with a confirmed diagnosis of panic-related anxiety will be randomized at stage two. Masked follow-up assessments will be conducted by an independent evaluator at 1, 3, 6, and 12 months (See Fig. 2). We will follow the Consolidated Standards of Reporting Trials (CONSORT) guidelines for designing and reporting of randomized parallel-group non-pharmacologic intervention trials [37–39]. The trial protocol follows the SPIRIT recommendations and has been registered at clinicaltrials.gov (NCT03632356, 15 August 2018, current protocol version 4.0 dated 21 February 2019).

